## Abstract

**Background:**

A standard of prehospital care for patients presenting with ST-segment elevation myocardial infarction (STEMI) includes prehospital 12-lead and advance Emergency Department notification or prehospital bypass to percutaneous coronary intervention centres. Implementation of either care strategies is variable across communities and neither may exist in some communities. The main objective is to compare prehospital care strategies for time to treatment and survival outcomes as well as cost effectiveness.

**Methods/Design:**

PREDICT is a multicentre, prospective population-based cohort study of all chest pain patients 18 years or older presenting within 30 mins to 6 hours of symptom onset and treated with nitroglycerin, transported by paramedics in a number of different urban and rural regions in Ontario. The primary objective of this study is to compare the proportion of study subjects who receive reperfusion within the target door-to-reperfusion times in subjects obtained after four prehospital strategies: 12-lead ECG and advance emergency department (ED) notification or 3-lead ECG monitoring and alert to dispatch prior to hospital arrival; either with or without the opportunity to bypass to a PCI centre.

**Discussion:**

We anticipate four challenges to successful study implementation and have developed strategies for each: 1) diversity in the interpretation of the ethical and privacy issues across 47 research ethics boards/commiittees covering 71 hospitals, 2) remote oversight of data guardian abstraction, 3) timeliness of implementation, and 4) potential interference in the study by concurrent technological advances. Research ethics approvals from academic centres were obtained initially and submitted to non academic centre applications. Data guardians were trained by a single investigator and data entry is informed by a detailed data dictionary including variable definitions and abstraction instrucations and subjected to error and logic checks. Quality oversight provided by a single investigator. The window of the trial in each community has been confirmed with the basehospital medical director to correspond to the planned technological advances of the system of care. We hope this comparative analysis across treatment strategies for clinical outcomes and cost will provide sufficient evidence to implement the superior strategy across all communities and improve outcomes for all STEMI patients.

**Trial registration:**

ClinicalTrials.gov: NCT00747656

## Background

Cardiovascular disease accounts for more deaths than any other disease and ischemic heart diseases, such as acute myocardial infarction (AMI), account for a large proportion of these deaths [1-3]. Timely recognition and reperfusion are life saving interventions [3-7]. Randomized controlled trials have demonstrated the superiority of prehospital fibrinolysis [8-11]; whereas other interventions such as 12-lead [12-15] and bypass to interventional hospitals [6,16-23] have not been subjected to the same rigorous analysis. Based on associations with improved time to treatment, 12-lead ECG and bypass to an interventional hospital has been implemented in many communities which makes it difficult to conduct a controlled trial. In contrast, many rural and urban communities with small volumes may not have implemented any one of these interventions, as such the standard of care for patients presenting with ST-segment elevation myocardial infarction (STEMI) varies between communities[24]. In 2004, the expert panel of Cardiac Care Network of Ontario report recommended that urgent angioplasty should be adopted as the standard of care[24]. Concurrent with this report the Ontario Health Technology Advisory Committee (OHTAC), upon their review of the literature regarding primary angioplasty for the treatment of STEMI, recommended that "every effort should be made to decrease the access time for patients with AMI from onset to symptoms to administration of fibrinolysis or primary angioplasty"[25,26]. This study is being conducted to evaluate different implementation strategies in place currently that could reduce symptom to intervention time in Ontario[25]. The objective of this paper is to describe the design of a study to compare these strategies against time to treatment and survival outcomes as well as cost effectiveness. We hope that this prospective cohort trial will promote the adoption of the optimal implementation strategy into the healthcare system and may provide the information required to directly change health policy and funding for systematic multidisciplinary care involving local EMS systems. We anticipate that the identification and implementation of the best care strategy may provide consistent and optimal care of patients presenting with STEMI across all communities in Ontario,

## Methods/Design

### Study Design

PREDICT is a prospective, population-based cohort study of four patient care strategies provided by regional EMS services to patients with chest pain and suspected ischemia.

1. 3-lead PHECG and transported to the nearest receiving ED who were not eligible for bypass based on transport time.

2. 3-lead PHECG and transported to the nearest receiving ED who were eligible for bypass based on transport time, if 12 lead PHECG was possible.

3. 12-lead PHECG and prehospital notification transported to the nearest receiving ED who were not eligible for bypass to a PCI center based on transport time.

4. 12-lead PHECG with prehospital notification and eligible for bypassing the nearest receiving ED with transport to a PCI center.

Bypass eligibility was based on transport distance of patients from their pick-up location to PCI center and the cut-off point was 60 kilometres.

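### As worded, the two 12-lead groups require prehospital notification and the 3-lead groups do not, so some STEMI patients of 12-lead services fit no group and the primary comparison has two readings

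*Protocol article*

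**What the plan says.** The four groups are defined in one place, the numbered list under Study Design in the protocol article. The lead-in calls them "four patient care strategies provided by regional EMS services to patients with chest pain and suspected ischemia". The list then reads:

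- Group 1: "3-lead PHECG and transported to the nearest receiving ED who were not eligible for bypass based on transport time".
- Group 2: "3-lead PHECG and transported to the nearest receiving ED who were eligible for bypass based on transport time", with the rider that this supposes a 12-lead had been possible.
- Group 3: "12-lead PHECG and prehospital notification transported to the nearest receiving ED", for patients whose transport time rules out bypass.
- Group 4: "12-lead PHECG with prehospital notification and eligible for bypassing the nearest receiving ED with transport to a PCI center".

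The Methods/Design part of the abstract describes the same strategies more loosely, as "either with or without the opportunity to bypass to a PCI centre". It also attaches a pre-arrival alert to dispatch to the 3-lead strategy. The primary outcome is the proportion reperfused within the target door time, compared across these four strategies.

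**The concern.** Notification is something that happens, or fails to happen, after the patient has come under a 12-lead service. Making it a condition of membership in groups 3 and 4 only means that, on the literal text, the 12-lead groups are selected on a post-exposure event and the 3-lead groups are not.

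The contrast is sharpest between groups 2 and 4. Group 2 rests on hypothetical eligibility ("who were eligible for bypass based on transport time, if 12 lead PHECG was possible"), so it keeps its patients whatever followed the choice of hospital. Group 4, its counterpart, is worded by notification and by transport to a PCI centre.

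If the patients without a group are left out, and if they reach target less often than notified patients, the 12-lead and bypass results look better than the strategies are. That would bear directly on the policy and funding decisions the article hopes to inform. Adjustment would not help: no covariate in Table 3 records recognition or notification, and regression cannot restore patients who were never assigned.

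**Working it through.** **Step 1: where each kind of STEMI patient falls on the literal wording.**

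| Patient | Group as worded |
|---|---|
| 3-lead, nearest ED, not bypass-eligible | 1 |
| 3-lead, nearest ED, would have been bypass-eligible | 2 |
| 12-lead, notified, nearest ED, not bypass-eligible | 3 |
| 12-lead, notified, bypass-eligible, taken to PCI centre | 4 |
| 12-lead, not notified | none |
| 12-lead, notified, bypass-eligible, taken to nearest ED | none |

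No section says where the last two rows are counted. They would be found, because Patients Enrolment has every ambulance call report screened.

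**Step 2: the plan's own figures.** Table 2 gives 402, 185 and 106 per arm for 37.4% against 47.4%, 52.4% and 57.4%. The two-proportion formula with pooled variance, two-sided alpha 0.05, 80% power and continuity correction gives 402, 185 and 107. Without the correction it gives 383, 172 and 97. Table 2 therefore reproduces to within one patient and is not in question. I use its 37.4% and 57.4% as anchors only.

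**Step 3: illustration with no true benefit.** Let m be the share of 12-lead STEMIs not notified and q their on-target rate. Neither is in the documents; I assume m = 10-30% and q = 20-37.4%. If the whole 12-lead arm is at 37.4%, the rate among notified patients is

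(37.4 − m × q) / (1 − m).

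With q = 20%:

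- m = 10%: (37.4 − 2) / 0.9 = 39.3%, a spurious gain of 1.9 points.
- m = 20%: (37.4 − 4) / 0.8 = 41.75%, a gain of 4.35 points.
- m = 30%: (37.4 − 6) / 0.7 = 44.9%, a gain of 7.5 points.

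With q = 37.4% the gain is exactly 0 for every m. At the planned 100 per group, the chance of a significant result in favour of 12-lead (uncorrected test, nominally 2.5% in that direction) becomes 4.7%, 9.1% and 18.6% in the three q = 20% cases.

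**Step 4: illustration with a real benefit.** If notified patients reach 57.4%, the difference from 37.4% with all 12-lead STEMIs kept is

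(1 − m) × 57.4 + m × q − 37.4.

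| m | q = 37.4% | q = 20% |
|---|---|---|
| 10% | 18.0 points | 16.3 points |
| 20% | 16.0 points | 12.5 points |
| 30% | 14.0 points | 8.8 points |

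The notified-only comparison shows 20 points in every row. Power at 100 per group (uncorrected) is 81% for 20 points. For the q = 37.4% column it is 73%, 62% and 51%.

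**The case against.** The strongest reply is that this turns condensed wording into an exclusion rule that the article never states. Much of it stands:

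- The only listed exclusion is age under 18, and all call reports are screened for eligible cases.
- The lead-in to the list assigns strategies to EMS services and to patients with suspected ischaemia, before STEMI is confirmed. The Discussion speaks of sites moving from 3-lead to 12-lead, and the abstract speaks of an opportunity to bypass.
- The STEMI identification outcome compares field readings of all STEMI subjects with a gold standard, so missed STEMIs appear to remain study subjects. Access to Interventions compares direct bypass with transfer across groups, which sits badly with bypass as an entry condition.
- The closing phrase of group 4 can be parsed as what the patient is eligible for, rather than as what happened.
- Groups 1 and 2 are also worded by care given (3-lead, nearest ED), and the abstract names an alert on the 3-lead side too. The asymmetry in the operative list lies in notification and, for group 4, destination.
- No section says what triggers notification. That it depends on recognising the STEMI in the field is an inference.

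A reader might go further and infer that missed STEMIs are in fact dropped from the 12-lead groups, that every 3-lead STEMI is kept, and that the result is therefore flattered. The documents do not support that.

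The reply does not, however, remove the notification condition from groups 3 and 4 or give the unplaced patients a group. Nor is this merely detail left to a fuller document: the article states the group definitions, and its other sections pull against them.

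**Conclusion.** The concern holds as a badly fixed exposure definition with two defensible readings. The literal one conditions the 12-lead groups on notification (and group 4 on transport to a PCI centre); the service-level one does not. They give different primary estimates whenever notified and non-notified patients differ in their on-target rate.

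The direction of bias, towards 12-lead and bypass, depends on two conditions that the documents do not settle: that the literal reading is followed, and that non-notified patients reach target less often. The size cannot be computed from the documents. Under the assumptions in the working it is 0 to 7.5 points when there is no true benefit. It is sensitive to those assumptions: at m = 30% and q = 10% it would be (37.4 − 3) / 0.7 − 37.4 = 11.7 points. It is not established that any bias will occur, but the definition should be settled before analysis because it determines who is in the primary comparison.

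**What to change.** State that, for the primary analysis, every confirmed STEMI is assigned by the ECG capability of its EMS service on the episode date (3-lead, or 12-lead with a notification programme), crossed with bypass eligibility by the pick-up distance rule under Study Design. Assignment should hold whether or not a 12-lead was acquired, notification was made or bypass took place. Report the comparison by care received as secondary, and give the number of patients in each service-level group who were not notified or not bypassed.

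The cost is a rewording of the group definitions. The patients are already captured by the call-report screening, and service capability by date should be available from the participating services. The drawback is that the apparent 12-lead effect may be smaller, with less power at 100 per group to detect it, as Step 4 of the working illustrates.

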### Inclusion and Exclusion Criteria

#### Inclusion criteria

○ Patients who call 911, and are:

○ Suspected by the paramedics to have ischemic chest pain for greater than 30 minutes but less than 6 hours, and

○ 18 years of age or older

○ Experiencing chest pain that fails to resolve with nitrates given as per protocol

#### Exclusion Criteria

○ Age < 18 years of age

### Setting

This study is set in regions of Ontario with a population of 3,043,853 served by 14 EMS services, under the medical control of 4 regional Base Hospital programs (Table 1)[27]. These regions represent 25% of the population of Ontario and 9.6% of the population of Canada. This geographic region covers 206,727 km^2 ^with variable population densities from 0.6 to 574 persons per km^2 ^representing rural, suburban, urban, and metropolis areas[27].

**Table 1 T1:** List of regional base hospital programs and emergency medical services participating in PREDICT study

Regional Basehospital Programs	Participating Emergency Medical Services (EMS)
Hamilton Health Sciences Centre for Paramedic Education & Research - Hamilton	County of Brant Ambulance Service Haldimand EMS Hamilton EMS Hamilton-Wentworth Regional Ambulance Service Norfolk EMS Six Nations Ambulance Service

North-East Ontario Regional Base Hospital Program - Sudbury	Algoma EMS Manitoulin-Sudbury EMS Sudbury EMS Sault Ste. Marie EMS Timmins EMS

Northwest Region Base Hospital Program	Superior North EMS

Sunnybrook Osler Centre for Prehospital Care - Toronto	County of Simcoe Paramedic Services, Peel Regional Paramedic Services

### Sample Size Calculation

The recruitment goal is to enrol 100 STEMI prospective subjects per group (e.g. as in the WEST trial)[28], for a total of 400 STEMI subjects. The primary estimate is based on a difference in the proportion of patients who received reperfusion (fibrinolysis or PCI) within target door-to-intervention times. We based our calculation using estimates from Canto et al., 2002[29]. In that study there was an increase in the percentage of the patients who received lytic therapy within 30 minutes, from 31% to 50% (an absolute difference of 19%). The percentage of patients who received PCI within 90 minutes increased from 29% to 48% (an absolute difference of 19%). Furthermore there was a combined 24% higher odds of receiving fibrinolytic therapy or PCI with the active EMS involvement (odds ratio 1.24, 95% CI 1.21 to 1.28, p < 0.001). Calculations were conducted using PASS software, assuming an alpha (α) of 0.05 and power of 80% (Table 2).

**Table 2 T2:** Sample size calculation for the PREDICT study

Baseline %	Intervention %	Absolute Difference	Odds Ratio	Number per arm
37.4	47.4	10%	1.5	402

37.4	52.4	15%	1.8	185

37.4	57.4	20%	2.3	106

To estimate the number of potential subjects that could be enrolled in the study, the annual rate of STEMIs that would occur within a 60 minute transport time of the closest PCI centre was determined. The surrounding areas within 60 minutes of a PCI centre were first identified using data from a Cardiac Care Network of Ontario (CCN) report published in 2004[6]. Current population estimates were then assigned to each of the surrounding areas using population estimates for 2006[27]. For counties or regions where a proportion of the population resided outside a 60 minute radius, population data from the 2006 Canadian census was used from the census subdivisions to adjust the 2006 population estimates[27]. To determine the rate of STEMI, an estimate of 571 per 1,000,000 inhabitants was calculated by taking an estimate obtained using CIHI data of 6524 STEMIs in Ontario for fiscal 2001/02 and dividing it by the 2006 Ontario Census Population and determining the rate per million inhabitants[6,27]. The number of potential subjects to be entered in per year was then estimated by assuming a 50% transport by EMS rate and a potential recruitment rate of 70%.

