### Analysis Plan

The primary outcome, and treatment time intervals, will be analyzed with one-way ANOVA and subsequent pair-wise multiple comparison procedures across the four treatment strategies. Different covariates (Table 3) will be analyzed using multiple linear regressions and they will be introduced into the model and evaluated as potential confounders. Variables will be retained if they have had an effect of 5% or greater on the coefficients for door-to-reperfusion time. Survival at 30 days and one year for STEMI patients will be analyzed as a binary outcome (Chi square) and as a survival analysis. Covariates that may affect survival will be analyzed with a Cox PH Regression Model. Adverse event rates will be analyzed with a Chi square analysis or a Fisher's exact test.

**Table 3 T3:** Analysis Plan - List of Covariates

1. Presence of cardiac catheterization lab in the primary destination hospital with the ability to perform 24-7 emergent primary angioplasty;
2. Fully affiliated teaching hospital;
3. Is the ED on Time Consideration (TC) or deferral from ambulances based on workload of acutely ill or injured patients?
4. Is the ED on Consideration (C) or deferral from ambulances based on workload?
5. Weekday;
6. Weekend;
7. Time of day in 8 hour intervals (08:00-16:00, 16:00-24:00, 24:00-08:00);
8. Age (as a continuous variable);
9. Sex;
10. History of MI;
11. History of CABG;
12. History of angioplasty;
13. Location of STEMI (anterior, posterior, inferior);
14. Off load delay (minutes);
15. PCA or PCI or bypass surgery.

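### At 100 per group, a specified 20-point pairwise difference has about 52–60% power after adjustment for six pairs, because Table 2 sizes only one unadjusted two-group test and no row of it supports 100

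*Protocol article*

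**What the plan says.** All sizing statements are in the Sample Size Calculation section of the protocol article.

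- The goal: "The recruitment goal is to enrol 100 STEMI prospective subjects per group", "for a total of 400 STEMI subjects". Another trial is cited as the precedent for 100.
- The calculation: "Calculations were conducted using PASS software, assuming an alpha (α) of 0.05 and power of 80% (Table 2".
- Table 2 has three rows, all from a 37.4% baseline. The most favourable reads "37.4 57.4 20% 2.3 106" (baseline, intervention, difference, odds ratio, number per arm). The next reads "37.4 52.4 15% 1.8 185". The 10-point row needs 402 per arm.
- The effects on which the calculation is said to rest come from a cited study: for fibrinolysis within 30 minutes, "from 31% to 50% (an absolute difference of 19" points; for PCI within 90 minutes, 29% to 48%, also 19 points.

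The Primary Outcome section compares the proportion reperfused within target time across all four strategies. The Analysis Plan starts with an overall one-way ANOVA, followed by "subsequent pair-wise multiple comparison procedures across the four treatment strategies".

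**The concern.** Three stated items do not fit together.

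1. The goal of 100 is below every number in the only table offered to support it.
2. Each row of that table compares one baseline with one intervention proportion at the full 5% level. The analysis compares four groups pairwise, and the sizing makes no allowance for that.
3. The text quotes baselines of 29% and 31% and 19-point effects. The table uses 37.4% and has no 19-point row.

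The study is meant to identify a superior strategy and to inform policy and budgets, so its conclusions will be pairwise. A reader who carries the 80% figure over to a non-significant pairwise result would give that result more weight than 100 per group supports.

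**Working it through.** **Inputs.** From the Sample Size Calculation section: 100 per group, four groups, alpha 0.05, power 80%, the Table 2 proportions, and the quoted 31% to 50% and 29% to 48%. Derived: 4 × 3 / 2 = 6 pairs. Assumed: two-sided testing (sidedness is not stated), and Bonferroni or Tukey as the adjustment (no procedure is named).

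**Step 1: reproduce Table 2.** With d = p2 − p1 and p̄ the mean of the two proportions:

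n0 = [1.960 √(2p̄(1−p̄)) + 0.8416 √(p1(1−p1) + p2(1−p2))]² / d²

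Continuity-corrected: n = (n0/4) [1 + √(1 + 4/(n0 d))]²

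For 37.4% vs 57.4%: p̄ = 0.474, and the square roots are √0.49865 = 0.7062 and √0.47865 = 0.6918. So n0 = (1.3840 + 0.5823)² / 0.04 = 96.7, and n = 24.17 × (1 + √1.2069)² = 106.4.

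| Difference | Table 2 | Corrected | Uncorrected |
|---|---|---|---|
| 10 points | 402 | 401.9 | 382.2 |
| 15 points | 185 | 184.5 | 171.4 |
| 20 points | 106 | 106.4 | 96.7 |

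The corrected column matches. The uncorrected column does not, and neither does a one-sided test (77 for 20 points, or 86 with correction). Table 2 is therefore a single two-group, two-sided 5% test with continuity correction.

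**Step 2: power at 100 per group, 37.4% vs 57.4%.** Power = Φ{(d − k − c × 0.07062) / 0.06918}. Here 0.07062 = 0.7062/√100, 0.06918 = 0.6918/√100, and k = 1/100 with correction or 0 without.

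| Procedure | Critical value c | Corrected | Uncorrected |
|---|---|---|---|
| One unadjusted test | 1.960 | 0.772 | 0.813 |
| Tukey, four groups, 396 error df | 2.580 | 0.545 | 0.602 |
| Bonferroni, 0.05/6 | 2.638 | 0.521 | 0.578 |

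For example, the corrected Bonferroni entry is (0.19 − 0.1863)/0.06918 = 0.053, and Φ(0.053) = 0.521.

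**Step 3: the quoted 19-point effects, by the same formulas.** Numbers in brackets are without the continuity correction.

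| Effect | Needed per arm, 80% power | Power at 100, one test | Power at 100, Bonferroni |
|---|---|---|---|
| 31% vs 50% | 113.9 (103.6) | 0.741 (0.786) | 0.482 (0.540) |
| 29% vs 48% | 112.1 (101.8) | 0.748 (0.793) | 0.491 (0.550) |

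**Step 4: detectable difference.** Setting the step 2 power to 0.80 and solving for d from a 37.4% baseline gives 20.7 points for one unadjusted test (19.7 uncorrected). Under Bonferroni it gives 25.4 points (24.4 uncorrected), which is larger than any row of Table 2.

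**Step 5: overall four-group test.** This uses a chi-square test on 3 df with noncentrality λ = 100 Σ(pi − p̄)² / [p̄(1 − p̄)], where p̄ is now the mean of all four proportions.

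- One group at 57.4%, three at 37.4%: λ = 100 × 0.03 / 0.2442 = 12.28, power 85%.
- Two groups at each level: λ = 100 × 0.04 / 0.2493 = 16.04, power 93%.
- 37.4%, 47.4%, 47.4%, 57.4%: λ = 100 × 0.02 / 0.2493 = 8.02, power 66%.

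**The case against.** **The plan never says that 100 per group gives 80% power.** The 80% belongs to the Table 2 calculations, the 100 is a recruitment goal with its own precedent, and no row is declared the target. A reader might infer a false power claim, but the text does not make one. What stands is that the goal and the calculation are set side by side with nothing to link them, and that no row supports 100.

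**The 100-versus-106 gap is small and depends on the method.** Without the continuity correction, 97 per arm is enough for the 20-point row and 100 gives 81%. This is right, and on its own the gap would matter little. For the quoted 19-point effects, 100 falls short either way, but only by about one percentage point of power when uncorrected.

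**The overall test comes first and is better powered.** This also stands. It would be wrong to say that the study as a whole is close to a coin-flip. The overall test has 66–93% power for patterns spanning 20 points. If one group differs by 20 points, simulation gives about an 82% chance that at least one of the three true pairs is significant even under Bonferroni (uncorrected). The low figures apply to one pair specified in advance.

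**No procedure is named, and that choice can be left to an analysis plan.** So 52% is the low end and not a property of this plan. In uncorrected simulations with one or two groups differing by 20 points, Holm gives a little over 60% for a specified pair. Pairwise tests protected only by the overall test give 77–81%, but do not fully control the familywise error with four groups. The point here is not that a method is missing; it is that the sizing ignores a pairwise analysis the article already commits to.

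**Two further inferences are not supported.** Six unadjusted tests would give about a 20% chance of at least one false positive, but the Analysis Plan calls for multiple comparison procedures, so that is not a consequence of the plan as written. The 37.4% baseline is unexplained, but the cited study is not at hand, so it cannot be called wrong.

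**Conclusion.** The point holds as a mismatch between the stated sizing and the stated analysis. Table 2 reproduces as one two-group test at the full 0.05, no row of it supports 100 per group, and six pairwise comparisons are planned. At 100 per group:

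- one unadjusted 20-point comparison has 77–81% power, and the quoted 19-point effects have 74–79%;
- a specified 20-point pair has about 52–60% after Bonferroni or Tukey adjustment;
- the pairwise difference detectable with 80% power under Bonferroni is 24–25 points;
- the overall test has 66–93%, or 85% if one group differs.

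Each range reflects use or not of the continuity correction, together with the procedure, the quoted effect or the pattern of proportions where these vary. The figures assume equal groups of 100, two-sided tests, and a 37.4% baseline except for the 19-point effects. They do not show that enrolment must rise. Since the remedy is restated text and the main first-stage test is reasonably powered for several patterns, this is a should-fix.

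**What to change.** In the Sample Size Calculation section, keep 100 per group and state what it delivers:

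- the power of the overall four-group test under named patterns (for example 85% if one group differs by 20 points, 66% for the graded pattern);
- about 77–81% for a single unadjusted 20-point comparison, saying whether a continuity correction is used;
- about 52–60% for a specified 20-point pair after familywise adjustment, narrowed to one figure once the procedure is named;
- a detectable pairwise difference of about 24–25 points at 80% power under Bonferroni.

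Also reconcile the 37.4% baseline in Table 2 with the quoted 29% and 31%, or give its source.

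The cost is a less favourable stated figure and a few sentences of text. No additional patients are needed. Naming a smaller set of primary contrasts would recover some power but leave other comparisons outside the primary analysis; that is a choice for the investigators and not part of this correction.

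### The sample-size table does not use the rates the text says it is based on, and 100 per group falls slightly short of 80% power on either set of figures

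*Protocol article*

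**What the plan says.** All of the sizing is in the Sample Size Calculation section of the protocol article.

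- The goal is 100 STEMI patients in each of four groups, 400 in all. The figure of 100 is given with a reference to another trial.
- The planning rates are said to come from one cited study. For lysis it reports an "increase in the percentage of the patients who received lytic therapy within 30 minutes, from 31% to 50% (an absolute difference of 19" points. For PCI: "The percentage of patients who received PCI within 90 minutes increased from 29% to 48% (an absolute difference of 19" points.
- The same study is then quoted for a "combined 24% higher odds of receiving fibrinolytic therapy or PCI with the active EMS involvement (odds ratio 1.24, 95% CI 1.21 to 1.28".
- On method: "Calculations were conducted using PASS software, assuming an alpha (α) of 0.05 and power of 80"%. Sidedness and continuity correction are not stated.
- Table 2 has three rows, each with a 37.4% baseline and gains of 10, 15 and 20 points, giving 402, 185 and 106 per arm. The last row reads "37.4 57.4 20% 2.3 106".

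The Primary Outcome section compares the proportion reperfused within target time (90 minutes for PCI, 30 for lysis) across the four strategies.

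**The concern.** The text and the table do not agree. The text names a source and gives its baselines, 31% and 29%. The table uses a third baseline for which no origin is given. The text gives a 19-point gain; the table has no 19-point row. The enrolment goal matches no row and is smaller than all of them.

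A reader will naturally attach the 80% to the 100 per group, since that is the size the trial will have. If 100 does not give 80% for the effect the text describes, a null pairwise result will be read as somewhat stronger evidence than it is. The odds ratio of 1.24 adds to the confusion. It stands beside the timeliness rates as if it supported the same effect, but as described it is for a different endpoint.

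**Working it through.** **Inputs.** From the Sample Size Calculation section: alpha 0.05, power 80%, 100 per group, the cited pairs 31/50 and 29/48, and the Table 2 pairs 37.4/47.4, 37.4/52.4 and 37.4/57.4. Assumed: two-sided test, equal independent groups, one pairwise comparison without multiplicity adjustment.

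**Formulas.** With d = |p1 − p2|, p̄ = (p1 + p2)/2, z = 1.960 and 0.842:

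- uncorrected: n0 = [1.960·√(2p̄(1−p̄)) + 0.842·√(p1(1−p1) + p2(1−p2))]² / d²
- continuity-corrected: n = (n0/4)·[1 + √(1 + 4/(n0·d))]²
- corrected power at n per group: Φ{[d − 1/n − 1.960·√(2p̄(1−p̄)/n)] / √([p1(1−p1) + p2(1−p2)]/n)}; without correction, omit 1/n.

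**Step 1: reproduce Table 2.**

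| Pair | n0 | corrected n | Table 2 |
|---|---|---|---|
| 37.4 / 47.4 | 382.2 | 401.9 | 402 |
| 37.4 / 52.4 | 171.4 | 184.5 | 185 |
| 37.4 / 57.4 | 96.7 | 106.4 | 106 |

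The two-sided corrected formula gives the table. One-sided, uncorrected, unpooled and arcsine versions do not. The table's arithmetic is sound.

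**Step 2: can 37.4% come from the cited baselines?** A weighted average 31w + 29(1 − w) with w between 0 and 1 lies between 29% and 31%. So it cannot.

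**Step 3: numbers needed on the cited rates, same method.**

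- 31/50: p̄ = 0.405; n0 = (1.960·0.6942 + 0.842·0.6811)²/0.19² = 103.6; corrected n = 113.9, about 114.
- 29/48: n0 = 101.8; corrected n = 112.05, about 112 (113 if rounded up).

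**Step 4: power at 100 per group.** For 31/50, corrected: (0.19 − 0.01 − 0.1361)/0.0681 = 0.645, and Φ(0.645) = 0.741.

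| Pair | corrected | uncorrected |
|---|---|---|
| 31 / 50 | 74.1% | 78.6% |
| 29 / 48 | 74.8% | 79.3% |
| 37.4 / 57.4 | 77.2% | 81.3% |

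**Step 5: where the shortfall comes from (corrected power).**

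- 37.4/57.4 at 106 per group: 79.8%.
- The same pair at 100 per group: 77.2%. Going from 106 to 100 costs 2.6 points.
- 19 points instead of 20, still from 37.4% (37.4/56.4): 72.6%. This costs a further 4.6 points.
- Replacing 37.4% by the cited baselines: 74.1–74.8%. This gives back 1.5 to 2.2 points.

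The baseline therefore works in the cautious direction. At a fixed 20 points, baselines of 29–31% need 102–104 per arm, against 106 from 37.4%.

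**Step 6: difference detectable with 80% power at 100 per group (corrected).** 20.2 points from 29%, 20.4 from 31% and 20.7 from 37.4%, so about 20 to 21 points.

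**Step 7: the odds ratio.** The cited timeliness pairs have odds ratios of (0.50/0.50)/(0.31/0.69) = 2.23 and (0.48/0.52)/(0.29/0.71) = 2.26. These agree with the 20-point row (2.26, printed as 2.3). The quoted 1.24 matches no row; the table's smallest odds ratio is 1.5.

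**The case against.** The strongest reply is that little is wrong. Table 2 is correctly computed. It is a grid of 10, 15 and 20 points, and rounding 19 to 20 in such a grid is ordinary. The 80% is attached to the table's own numbers, not to 100 per group, which is credited to another trial. The 37.4% baseline asks for more patients than the cited rates would. Without continuity correction, power at 100 is 79% to 81%. And Table 2 already shows that smaller effects need many more patients.

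Most of this stands, and it limits the point to a modest one. What remains is that the text claims a basis its table does not use, and that no power is given for the size actually planned. Having chosen the corrected method for Table 2, the plan should be judged by it at 100 as well.

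A reader might infer three stronger things that the document does not support:

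- *That the 19-point gain contrasts EMS with non-EMS patients and so cannot apply here.* All PREDICT patients enter through EMS ("Patients who call 911, and are" in the inclusion criteria). But active EMS involvement is named only in the sentence on the odds ratio and is not defined there. The section does not say which groups the 31/50 and 29/48 rates compare, and the cited study is not at hand.
- *That the true planning effect is an odds ratio of 1.24, so the trial is far too small.* No row of Table 2 uses it, and it is for another endpoint.
- *That 12-lead versus 3-lead overall has only the power of 100 versus 100.* Two of the four strategies use 3-lead and two use 12-lead, so that question pools to 200 versus 200. From 37.4%, corrected power is then about 98%, 83% and 48% for 20, 15 and 10 points.

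**Conclusion.** The point holds as a mismatch between stated inputs, table and goal. The 37.4% baseline cannot be derived from the cited 29% and 31%. On the cited rates the plan's own method needs 112–114 per arm, not 106 or 100. Power at 100 per group is 74–75% for the cited rates and 77% for the most favourable row of Table 2. The gap to 80% is 3 to 6 percentage points with the correction; without it, the cited rates fall about 1 point short and the 20-point row reaches 81%. It arises from 19 versus 20 points and from 100 versus 106. The unsourced baseline is a fault of documentation and does not itself lower power.

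These figures assume a two-sided 0.05 test, equal independent groups and a single pairwise comparison. The Analysis Plan foresees pairwise multiple comparisons across four strategies; any adjustment for them would lower pairwise power further.

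**What to change.** In the Sample Size Calculation section:

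1. Either recompute Table 2 from the cited baselines of 29–31% and the 19-point gain (112–114 per arm by the present method), or give the source of 37.4%.
2. State the test behind Table 2 (two-sided, continuity-corrected).
3. For 100 per group, state the power (74–75% for the cited rates, 77% for 37.4% versus 57.4%) or the detectable pairwise difference (about 20 to 21 points), and say that this is for one unadjusted comparison.
4. Do not use the odds ratio of 1.24 as support for the timeliness effect.
5. State which groups the cited rates compare.
6. If 12-lead versus 3-lead overall is to be reported, compute its power on the pooled groups of 200.

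The cost is a short recalculation and a few sentences. Enrolment need not change. The only drawback is a slightly less favourable stated power.
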